#### Gamification and storytelling

The conversational agent named BEDDA will present the story in which BEDDA and the participant go on a treasure hunt. Since BEDDA's sailboat cannot be powered and steered by BEDDA alone, BEDDA asks the participant to power the boat by providing wind energy. BEDDA goes on to explain that at the end of their journey, when they collected 30 keys, a magic chest opens and the coins in it can be collected. BEDDA also explains that the magic chest has another magical power. Provided that the participant manages to collect all keys in less than 40 days, they have the chance to win even further coins (gamification—challenge [70]) or keep a smartwatch received at the beginning of the study (smartwatch group only). Second, if the participant needs more than 45 days to find all keys, the chest loses its magical power, and all gold coins disappear (gamification—challenge [70]). We included this time constraint due to the timescale of this study and to further motivate the participants.

As explained by BEDDA, 30 keys need to be found along the way (Fig. 4) that unlock a chest at the journey’s end (Fig. 5). These keys are hidden in bottles (Fig. 6) floating on the river on the daily trip. Besides the key, the bottle also contains the daily wisdom of the day. Each day, the participants can only find one key. Before and after each trip, BEDDA presents a map (Fig. 7) to the participants illustrating their progress (goal setting—complete a daily task [70]). The progress made is also indicated by an illustration of the number of keys collected and the days past since the journey started (gamification—progress indication or badges [70]). The participants can additionally interact with Breeze as often as they want on any given day, given that they have already completed the daily trip.

**Fig. 4 Fig4:**
[figure not shown]
Keys. Graphic illustration of the number of keys collected in the study. The number is increased after each interaction with Breeze. [name] created images specifically for this study as part of her employment at the Center for Digital Health Interventions. The Center for Digital Health Interventions holds the copywriter to all images

**Fig. 5 Fig5:**
[figure not shown]
Treasure. The chest with 30 locks the participant aims to open. [name] created images specifically for this study as part of her employment at the Center for Digital Health Interventions. The Center for Digital Health Interventions holds the copywriter to all images

**Fig. 6 Fig6:**
[figure not shown]
Bottle. Illustration of the bottle in which the daily advice and the keys are found. [name] created images specifically for this study as part of her employment at the Center for Digital Health Interventions. The Center for Digital Health Interventions holds the copywriter to all images

**Fig. 7 Fig7:**
[figure not shown]
Map. The map used to illustrate the progress of the participant. [name] created images specifically for this study as part of her employment at the Center for Digital Health Interventions. The Center for Digital Health Interventions holds the copywriter to all images

### Study design

Figure 8 shows the experimental design of the study. The study will run for 60 days, and participants will be randomly (using an algorithm on the recruitment website) allocated to one of four groups we listed in Table 1: intervention with smartwatch (IG_sw_), intervention without smartwatch (IG_nsw_), waitlist with smartwatch (WG_sw_), waitlist without smartwatch (WG_nsw_). The intervention part of the study will run for 30–45 days, depending on how many days the participant needs to finish the required 30 once-per-day guided interactions (described below). Participants allocated to the intervention group (IG_sw_ and IG_nsw_) will start the experiment first. In their first interaction (T_1_), they will receive the study information, give written informed consent via the app (type of content approved by the ethics committee), complete the initial assessment, receive a tutorial on how to use the app, and complete a training with Breeze for the first time. Participants allocated to the waitlist group (WG_sw_ and WG_nsw_) will complete the baseline assessment (T_0_) but will not yet start using the app for another 30 days. In these first 30 days, participants in the intervention group will interact daily with BEDDA. This interaction includes dialogues with the conversational agent, answering questions before and after Breeze, and conducting breathing training with Breeze. Each day, they can also choose whether they want to receive daily wisdom matching the symptom of the day. Additionally, the conversational agent moves the story further each day, and the app uses gamification elements to illustrate progress. On day 15 of the intervention, participants allocated to the intervention group will respond to the half-time assessment questions and on day 30, participants in the intervention group will respond to the final assessment.

**Table 1 Tab1:** Groups included in the study

Group	Treatment	Smartwatch	Planned N
IG_sw_	Intervention	Yes	25
IG_nsw_	Intervention	No	75
WG_sw_	Waitlist	Yes	25
WG_nsw_	Waitlist	No	75

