**Fig. 8 Fig8:**
[figure not shown]
Experimental Design. Experimental design of the study. *Note*: T_0_: Assessment at baseline for the control group only. T_1_: Start intervention with start interaction and assessment. T_2_: Half-time intervention with half-time interaction and assessment. T_3_: End of intervention with final interaction and assessment. Intervention: Daily engagement in the intervention consists of interaction with the conversational agent, Breeze, providing assessments, and receiving daily wisdom. Figure created by [name] as part of his employment at the Center for Digital Health Interventions

Participants assigned to the waitlist control group (WG_sw_ and WG_nsw_) will respond to baseline assessments (T_0_) on day 1 and 15 (corresponding to T_1_ and T_2_ in the intervention groups). On day 30 (T_3_ for the intervention group) the control group will start the intervention part of the study. The control group participants will be informed about the assessments, and the study starts through a notification on their smartphones. Participants in the control group will then complete the same intervention as the intervention group including the initial, half-time, and final assessment.

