#### Incentive mechanism

Participants will receive financial compensation for their participation if they meet certain criteria. First, participants need to interact with the app at least once per day on 30 days and complete the daily trip with the intervention. The participants can use Breeze more often on any given day, but 30 different days are needed to complete the intervention and be eligible for compensation. Second, participants need to complete the additional questions at baseline (T_0_, waitlist control group only), the start of the intervention (T_1_), the half-time (T_2_), and the final assessment (T_3_) within the once-per-day guided interaction. Third, participants must complete the intervention in 30–45 days to receive a compensation of 40 CHF. Participants needing more than 45 days will not receive any financial compensation. Forth, participants completing the intervention in 30–40 days have the chance to win additional monetary compensation in a raffle (ten times 100 CHF, ten times 200 CHF, five times 300 CHF). Participants in the smartwatch group are not eligible for this raffle but can keep the smartwatch if they complete the intervention in 30-40 days. Since we are not collecting any personal information about the participants enforcing participants with insufficient data to return the smartwatch is not feasible. However, we strongly urge the participant in the final interaction to return the smartwatch if they did not provide sufficient data.

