### Estimation of sample size

Sample size calculations for machine learning approaches, such as for objectives one and two, are less rigorously described compared to sample size estimations for investigation of efficacy. Therefore, we calculated the sample size needed for objective three and used this number of participants to estimate the expected correlation between features and outcomes for objectives one and two.

The third objective of our study is to investigate the efficacy of BEDDA. We operationalized this with three assessment times (at the start of the intervention, after 15 interactions, and after 30 interactions) in two groups (intervention and waitlist control). Assuming a small effect (Cohen’s d = 0.225), a power of 0.8, and an alpha level of.05, we calculated that we need at least 194 to detect an existing effect of BEDDA compared to control. Regarding our first and second objectives, we calculated that when 194 participants provide data, assuming a 0.05 alpha level and a power of 0.8, a Pearson moment correlation coefficient of 0.23 would be necessary for a significant result. Low et al. [22] reported a median number of participants for studies investigating voice changes in depression of 123 (with a range from 11 to 1688). With the estimated 194, we are above the mean but in a reasonable range.

Related work collecting data for the development of DBMs has reported a mean adherence rate of 86.6% [40]. Due to the extended assessment period, we assume a greater attrition rate. However, we also consider specific elements of our study (monetary incentives, storytelling, and gamification) that may lead to increased adherence. Considering these factors, we expect a dropout rate of approximately 20%, slightly greater than the dropout rate reported in related work [40]. Assuming this dropout rate, we aim to initially enroll 220 participants.

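### The PHQ-9 assessment clock is stated inconsistently and differs by arm: the intervention arm's T3 follows the 30th daily session (day 30 to 45), while the controls' follows the calendar (day 30)

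*Protocol article*

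**What the plan says.** **Intervention arm, session clock.** The sample-size section of the protocol article defines the efficacy design by "three assessment times (at the start of the intervention, after 15 interactions, and after 30 interactions"). The Fig. 8 legend defines the last assessment as "T_3_: End of intervention with final interaction and assessment". The Incentive mechanism section places "the final assessment (T_3_) within the once-per-day guided interaction". Only one session counts per day, 30 are needed, and the Study design section states: "The intervention part of the study will run for 30–45 days, depending on how many days the participant needs to finish the required 30" sessions.

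**Intervention arm, calendar clock.** The same Study design section also says that "on day 30, participants in the intervention group will respond to the final assessment", and puts the half-time assessment on day 15.

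**Waitlist arm.** The text under Fig. 8 sets assessments on days 1 and 15, matched to T1 and T2, and continues: "On day 30 (T_3_ for the intervention group) the control group will start the intervention part of the study". The third comparison value is therefore the initial assessment of the controls' own intervention, announced by a notification on the phone.

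**Analysis.** PHQ-9 is the primary distal outcome. Its first analysis is a two-way mixed ANOVA with two groups and three measurement times.

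**Duration.** "The study will run for 60 days".

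**The concern.** A 2 × 3 mixed ANOVA treats each measurement time as the same point for both groups. Here the intervention arm's second and third points depend on how fast a person completes sessions, while the controls' depend on the calendar. Two things follow.

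- **Unequal follow-up.** Any change in PHQ-9 that comes with time alone (term dates, natural improvement, regression to the mean after screening) is given more days to act in the intervention arm.
- **Adherence-dependent missingness in one arm.** The intervention T3 sits inside the 30th session, so it is scheduled only for those who get that far. The payment rules point the same way, because anyone who needs more than 45 days is paid nothing. The controls' third value requires only that they start.

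At stake is whether the primary randomised contrast compares like with like. An analysis plan can choose how to handle missing values, but it cannot recover a day-30 PHQ-9 that was never scheduled.

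**Working it through.** The plan gives no figure for assessment lag or for loss tied to session count, so there is nothing to reproduce on this point. Its N of 194 does not enter the argument.

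**1. The two clocks side by side (day 1 = start)**

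| Assessment | Intervention, session clock | Intervention, calendar wording | Waitlist |
|---|---|---|---|
| First | day 1 | day 1 | day 1 |
| Second | 15th session, day 15 at the earliest | day 15 | day 15 |
| Third | 30th session, day 30 to 45 | day 30 | day 30, at start of own intervention |

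The two intervention columns agree only for someone who misses no day. The 30-to-45-day allowance shows that the plan does not assume this.

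**2. Lag at T3.** 30 − 30 = 0 days at the least and 45 − 30 = 15 days at the most. The upper limit is 15/30 = 50% more follow-up.

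**3. How often would there be a lag? (illustration)** Assume that each day is completed independently with probability p, with the first session on day 1. The mean day of the k-th session is 1 + (k − 1)/p, and the chance that the 30th falls on day 30 is p^29.
- p = 0.866 (the adherence figure that the sample-size section cites from related work, borrowed here as a daily probability): T2 at 1 + 14/0.866 = day 17.2; T3 at 1 + 29/0.866 = day 34.5; 0.866^29 = 1.5% exactly on day 30.
- p = 0.95: T3 at day 31.5; 23% on day 30.
- p = 0.80: T3 at about day 37; 0.2% on day 30.

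If adherence varies between people (beta-distributed, mean 0.866, concentration 3 to 10), simulation gives 14 to 35% reaching T3 on day 30 and 5 to 12% not there by day 45. Those not there are the low adherers.

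**4. Timing component (illustration).** Bias = (time trend per 30 days) × lag/30. With an assumed trend of 0.1 to 0.3 SD per 30 days:
- lag 4.5 days: 0.015 to 0.045 SD
- lag 15 days: 0.05 to 0.15 SD

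**5. Missingness component (illustration).** If a share q of the arm lacks T3 and would have scored Δ SD worse than completers, the completers' mean differs from the full arm's mean by qΔ. Take q = 0.20, which is the plan's study-wide dropout figure applied here to one arm:
- Δ = 0.2: 0.20 × 0.2 = 0.04 SD
- Δ = 0.5: 0.20 × 0.5 = 0.10 SD
- Δ = 0.8: 0.20 × 0.8 = 0.16 SD

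If controls also lose a share q_c with gap Δ_c, the net bias is qΔ − q_cΔ_c. Equal selective loss cancels it.

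**6. What 0.10 SD would do.** In a two-sided 5% two-group comparison with n per arm, SE = √(2/n). For n = 80 (100 planned per arm less 20%), 0.10/0.158 = 0.63 and the true error rate is 9.7%. For n = 97 (194/2), 0.10/0.144 = 0.70 and it is 10.7%.

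**7. Study length.** Controls start on day 30 and have 30 to 45 days, so they end at about day 60 to 75. Sixty days leaves them none of the grace period that the payment rule allows.

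**The case against.** **The calendar reading has support.** The Study design section states days 15 and 30 for the intervention arm, the text under Fig. 8 equates day 30 with T3, and the Background describes severity as reported every two weeks. The design figures are not visible in the text at hand. This stands as evidence that the article contradicts itself. It does not restore a common clock, because three other sections tie the assessments to sessions and the same Study design section allows 30 to 45 days.

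**Controls can be late or missing too.** Their third value is collected when they open the app and begin their own intervention. A reader might infer that controls are assessed whatever they do, and the text does not support that. The asymmetry is between completing 30 sessions and starting one.

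**Lags may be short.** Reminders are planned, and the raffle or keeping the watch requires finishing within 40 days. At the borrowed adherence figure the mean lag is 4.5 days. This stands: the timing component is small unless lags are long or the time trend is marked.

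**Absence of T3 is an inference.** It follows from where T3 is placed. The article does not say whether lapsed participants are prompted, or whether T3 is still taken after day 45; it only withholds payment. Missing-data methods may be set out elsewhere, but the schedule is design, and this article fixes it.

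**Measuring after the full course is a legitimate aim.** That is true, but the contrast with a control measured at day 30 then needs a matching time.

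**Conclusion.** The concern holds as an inconsistent, arm-dependent assessment clock for the primary outcome. As written, the intervention T3 falls 0 to 15 days after the controls' third assessment, and none is scheduled for participants who stop before session 30. The planned ANOVA can be biased by unequal follow-up and by missingness tied to adherence.

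Size and direction cannot be derived from the documents. The 0.04 to 0.16 SD range assumes 20% missing in the intervention arm alone and a gap of 0.2 to 0.8 SD, for which the article gives no source. It shrinks if controls are selectively lost as well.

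Two stronger readings are tempting and should not be drawn:
- **That the bias favours BEDDA.** This is plausible if those who stop are doing worse, but nothing in the article shows that they are, and loss among controls could offset it.
- **That the bias is some 44% of the target effect (0.10/0.225).** This stacks an unsourced 0.5 SD gap on a study-wide dropout rate applied to one arm. It also takes 0.225 as Cohen's d. The stated N of 194 is reproduced only if 0.225 is Cohen's f (F test with 2 numerator df, noncentrality f²N, denominator df N − 3: power 0.801 at N = 194). Read as d, a two-sided comparison of two means needs 622 in total.

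The 60-day statement is a separate and minor inconsistency, and the bias argument does not rest on it.

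**What to change.** For objective 3, prompt PHQ-9, GAD-7 and TICS on calendar days 15 and 30, counted from the start (day 1), in both arms. Do this regardless of the number of sessions completed, include participants who have stopped the daily trips, and analyse everyone as randomised. Keep the session-triggered T2 and T3 for the biomarker work. Align the Study design section, the Fig. 8 legend, the Incentive mechanism section and the sample-size section with this one rule.

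Separately, reconcile the 60-day duration with a 30-day wait plus 30 to 45 days of intervention (about day 60 to 75).

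The cost is a scheduling rule in an app that already sends calendar notifications to controls. Slower participants answer extra questionnaires, and for them the day-30 effect reflects partial exposure. No sample-size figure changes. The rule has to be in place before data collection, because a missed day-30 value cannot be obtained later.

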**Fig. 8 Fig8:**
[figure not shown]
Experimental Design. Experimental design of the study. *Note*: T_0_: Assessment at baseline for the control group only. T_1_: Start intervention with start interaction and assessment. T_2_: Half-time intervention with half-time interaction and assessment. T_3_: End of intervention with final interaction and assessment. Intervention: Daily engagement in the intervention consists of interaction with the conversational agent, Breeze, providing assessments, and receiving daily wisdom. Figure created by [name] as part of his employment at the Center for Digital Health Interventions

Participants assigned to the waitlist control group (WG_sw_ and WG_nsw_) will respond to baseline assessments (T_0_) on day 1 and 15 (corresponding to T_1_ and T_2_ in the intervention groups). On day 30 (T_3_ for the intervention group) the control group will start the intervention part of the study. The control group participants will be informed about the assessments, and the study starts through a notification on their smartphones. Participants in the control group will then complete the same intervention as the intervention group including the initial, half-time, and final assessment.

#### Recruitment, inclusion criteria, exclusion criteria

A highly relevant group that shows alarming rates of symptoms of subclinical [80–83] and clinical depression are undergraduate [84], graduate [85], and Ph.D. students [86]. Our study aims at this population by recruiting participants from Swiss universities with no or subclinical symptoms of depression and anxiety. To increase the diversity of our sample, we plan to recruit participants from the general population as well. We will recruit participants via mailing lists of universities, social media, and other communication channels such as flyers and advertisements. Since participants may know each other spill-over effects could occur.

Participants must be at least 18 years old, not pregnant, not diagnosed with Asthma, COPD, or other respiratory conditions, and should be willing to invest approx. five minutes of their time per day for 30 days. We will use the 9-item version of the Patient Health Questionnaire Short Version (PHQ-9, [44]) for screening purposes to determine the severity of depression. We will also use the 7-item version of the General Anxiety Disorder Questionnaire (GAD-7, [87]) to assess the severity of anxiety. Participants with scores greater than 15 (more than mild symptoms) in either screening instrument will be excluded and directly referred to a mental health hotline for the general public and mental health services of universities. We will also exclude participants responding with “several days (+1)”, “more than half the days (+2)”, or “nearly every day (+3)” to the question of the PHQ-9 assessing suicidal or self-harm ideation, and we advise the participant to seek professional help immediately. We will not use minimal cut-off scores to exclude participants because it is difficult to determine at which point a participant shows sufficient symptoms to benefit from the intervention. Additionally, we expect a selection effect due to the advertisement content focusing on improving symptoms and severity of depression (e.g., one of the outlined potential benefits is “reduce stress”).

Furthermore, we will exclude participants with a current episode of a diagnosed mood disorder (Major Depressive Disorder, Bipolar Disorder, Persistent Depressive Disorder, or a Disruptive Mood Dysregulation Disorder). The same applies to participants with other diagnosed psychiatric disorders (e.g., Generalized Anxiety Disorder, Schizophrenia, Borderline Personality Disorder). Participants currently receiving psychotherapeutic or psychopharmacological treatment can not participate in the study.

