## Background

Despite effective pharmaceutical, therapeutic, and digital treatments [1], depression remains a global health problem [2] with rising prevalence [3]. Researchers worldwide aim to address this worrisome development by investigating and developing digital interventions, such as smartphone apps, to improve treatment and increase the availability of support. However, given the steady influx of new cases of depression [4], especially due to the Covid-19 pandemic [5, 6], climate change [7], and other world events such as the war in Ukraine, the focus on improving treatment and treatment availability alone may not suffice. It must be complemented by a commitment to improving prevention, i.e., aiding vulnerable individuals who already show weaker symptoms of depression (i.e., subclinical depression) or have biological, social, or environmental predispositions [8, 9].

Subclinical depression, also called minor or subsyndromal depression, is a milder form of depression characterized by less severe and present symptoms. For a diagnosis, an individual needs to report two to four criterion symptoms of depression with at least one of the core symptoms (depressed mood or anhedonia) over a period of two weeks [10, 11]. Evidence shows that many patients with subclinical depression still report persistent depressive symptoms after twelve months when left untreated and that subclinical depression poses a 10–20% risk of deteriorating into a major depressive disorder (MDD) and a 33–50% risk of patients developing moderate functional impairments [10–12].

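### The PHQ-9 exclusion rule can admit people with more depressive symptoms than the protocol's own definition of subclinical depression allows

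*Protocol article*

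**What the plan says.** All of this is in the protocol article.

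- *Recruitment, inclusion criteria, exclusion criteria* gives the target as people "with no or subclinical symptoms of depression and anxiety". The upper limit is "Participants with scores greater than 15 (more than mild symptoms) in either screening instrument will be excluded"; those people are referred to a hotline and to university services. There is deliberately no lower limit: "We will not use minimal cut-off scores to exclude participants".
- The same section excludes anyone who answers "several days (+1)”, “more than half the days (+2)”, or “nearly every day (+3" "to the question of the PHQ-9 assessing suicidal or self-harm ideation". This is the only place where item scores are given.
- It then excludes people with a current diagnosed mood disorder, another diagnosed psychiatric disorder, or current psychotherapeutic or psychopharmacological treatment.
- *Background* gives the requirement for subclinical depression: "an individual needs to report two to four criterion symptoms of depression with at least one of the core symptoms", over two weeks.
- *Study objectives* places the biomarker work (objectives 1 and 2) in the subclinical range. The Abstract words the efficacy aim (objective 3) for subclinical depression too.

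**The concern.** The limit is a total score and the definition is a count of symptoms. A total of 15 leaves room for more symptoms than the definition permits, so people outside the stated population can pass screening. Two things are at stake.

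- **Population.** The biomarker models and the efficacy estimate would be reported as findings in no or subclinical depression, although part of the sample might not meet that description.
- **Screening.** The same line decides who is referred. Someone with five to seven frequent symptoms and a total of 15 or less is not referred on the score and may be allocated to the 30-day wait.

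The remaining criteria depend on an existing diagnosis or treatment. *Enrollment and allocation* describes an online survey and no clinical interview. *Background* itself says that modest depression is the most likely to be missed. For an undiagnosed person, the score is therefore the main barrier.

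**Working it through.** **Inputs**

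- Eligible totals: 0 to 15 on each instrument (recruitment section).
- PHQ-9 item scores: 0, 1, 2, 3. The article gives +1 to +3 for the self-harm item; I assume the same scoring for all nine items.
- Self-harm item: must be 0, so an eligible total comes from 9 − 1 = 8 items.
- Definition: two to four symptoms, at least one of them core (*Background*). The article does not say at which item score a symptom counts as present, so both natural readings are shown.

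**Step 1. Single patterns, self-harm item at 0**

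- Five symptoms at +3: 5 × 3 = 15. This is not greater than 15, so the person is eligible.
- Seven symptoms at +2: 7 × 2 = 14, eligible.

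Both exceed four symptoms.

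**Step 2. Symptom present from +1**

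Four symptoms give at most 4 × 3 = 12. Every total of 13, 14 or 15 therefore has at least five symptoms.

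**Step 3. Symptom present from +2**

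Five symptoms need at least 5 × 2 = 10 points, so five or more are impossible up to a total of 9 and possible from 10. At 15, exactly four symptoms remain possible, for example four items at +3 and three at +1: 12 + 3 = 15.

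**Step 4. All response patterns**

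Enumerating the 4^8 = 65,536 patterns of eight items gives the share of patterns at each total that have five or more symptoms:

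| Total | Present from +1 | Present from +2 |
|---|---|---|
| 9 | 77.9% | 0% |
| 10 | 89.6% | 0.8% |
| 11 | 96.4% | 5.8% |
| 12 | 99.1% | 19.7% |
| 13 | 100% | 43.5% |
| 14 | 100% | 70.0% |
| 15 | 100% | 89.5% |

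If a core item must also be present, the +2 figure at 15 falls to 82.1%. These are shares of possible patterns, each counted once. They are not estimates of how many participants will be affected.

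**Step 5. One number on two scales**

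- PHQ-9: 15 / (9 × 3) = 15/27 = 56% of the maximum, or 15 / (8 × 3) = 15/24 = 62.5% of what an eligible person can score.
- GAD-7: 15 / (7 × 3) = 15/21 = 71%, assuming 0 to 3 scoring, which the article does not state.

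The article gives no severity bands for either scale, so neither percentage can be checked against the words in parentheses.

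**The case against.** **The definition is background, not a criterion.** It describes what a diagnosis needs, while eligibility rests on a severity score. That is true, but the eligibility section uses the word subclinical for its target, and the article defines it nowhere else. The mismatch stands.

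**Endorsed items are not criterion symptoms.** This stands in part. Totals of 13 to 15 all exceed four symptoms only if an item counts from +1. On the stricter count some of these people still fit the definition. Five items at +3 exceed it on either count.

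**Other exclusions narrow the group.** They do, but they remove only people already diagnosed or treated, plus anyone who endorses the self-harm item. The patterns in step 1 survive all of them unless the person has a diagnosis or is in treatment.

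**A reader might infer that the limit contradicts its own label.** The documents do not show this. Read literally, the parenthesis describes the scores above 15, and nothing in the article disputes that they are more than mild. The objection would need published bands for lower scores, which the article does not give. The label is unsupported, not contradicted.

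**A reader might extend the finding to anxiety.** The article defines no subclinical anxiety and gives neither GAD-7 bands nor GAD-7 item scoring. Using one number on scales of different length is a reason to check that limit, not a demonstrated error.

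**Conclusion.** The point holds for the PHQ-9. An upper limit of 15 can admit people with five to seven frequent depressive symptoms to a study whose target is no or subclinical symptoms, with subclinical set at two to four. The overlap covers totals of 13 to 15 in full if a symptom counts from +1, and totals of 10 to 15 in part if it counts from +2. The absence of a lower limit is deliberate, fits the stated target and is not at fault.

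This rests on 0 to 3 scoring for every PHQ-9 item. How many such people will enrol is unknown, because the article gives no expected score distribution. The finding is that they can be enrolled, not that they will be.

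A reader might also infer a biased treatment effect. The documents do not support that: both arms are randomised under the same criteria. What is affected is the population to which objectives 1 to 3 apply, and who is referred at screening.

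**What to change.** **Before recruitment.** The authors should reconcile three items: the limit for each instrument, the severity label attached to it, and the definition in *Background*. Alternatively, they should restate the population to which objectives 1 to 3 apply. Which item governs is a clinical decision, and no cut-off is proposed here. The GAD-7 limit should be checked at the same time, with the source of its label stated.

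**In the analysis.** Prespecify the PHQ-9 item score at which a symptom counts as present. Use the PHQ-9 items, which are already collected, to flag participants above the four-symptom limit. Report objectives 1 to 3 with and without them. Participants with no symptoms stay in both sets, because the article intends to include them.

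**Cost.** Criterion text and screening-page logic, one extra analysis set that is smaller and so less precise, and possibly slower recruitment if the eligible range narrows. No new data are needed.
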